### Procedure

A Norwegian website (www.bodyproject.no) has been designed to facilitate recruitment and project profiles are posted on Facebook and Instagram. The link will be shared via our online platforms, including Facebook, Instagram, and TikTok. Also, advertisement campaigns on social media will be run nationally. Individuals express interest by sending an e-mail to a *Body Project* mailbox hosted by Oslo University Hospital, which leads to a screening phone call to determine eligibility based on the inclusion criteria described above. In this screening call eligible participants verbally confirm to experience at least some body dissatisfaction. After providing informed consent, participants will complete baseline assessment (pretest) before being randomized into one of three arms: (i) peer-led virtual *Body Project* groups; (ii) clinician-led virtual *Body Project* groups; and (iii) educational video control group. Assessment will be repeated post intervention (posttest) and follow-up assessment after 6-months, 1-year, and 2-years. ED diagnostic interviews are conducted at baseline, 1-year, and 2-year assessments by research staff who are masked to the condition to which each participant will be randomized. Online assessment will be conducted via an online survey (Viedoc) hosted by Clinical Trials Unit (CTU), Oslo University Hospital. Randomization will be conducted by Viedoc once baseline assessment is completed. Virtually delivered *Body Project* group sessions will be implemented by use of Microsoft Teams, administered by Oslo University Hospital. Adaptations required for virtual script delivery include administration of home exercises via e-mail and using the chat function for summarizing themes during in-session group discussions rather than white boards or flip-charts used for in-person *Body Project* groups. This study is funded by the Norwegian Health Authority Region South-East (reference 2,023,032).

### Group facilitators

Clinician group facilitators consist of nurses (psychiatric and school health nurses), clinical dietitians, and a social worker, who are licensed health care personnel associated with the Regional Department for Eating Disorders at Oslo Universal Hospital. Peer group facilitators are recruited through acquaintances of our research team, and includes university and college-level students (not within medicine, psychology, or nursing) and maximum four years older than the participants.

### Training and supervision

Facilitators (both clinicians and peer educators) will read the intervention manual that outlines the theoretical rational of the intervention, reviews the evidence-base for the *Body Project*, and contains a detailed intervention script. Facilitators will then attend an 8-hour virtual workshop, where the conceptual rationale and supporting evidence for the *Body Project* are presented, facilitators role-play delivery of the intervention using the scripted manual, and process issues are discussed (e.g., promoting session attendance and homework completion, and recording attendance, homework completion, and verbal participation in the sessions for each group participant). All *Body Project* sessions will be videotaped, and all sessions from the first group implemented by facilitators will be rated for intervention fidelity and therapeutic competence (see below for psychometrics); supervision based on these ratings will be provided to facilitators via e-mail (feedback on what went well, and advice on how certain aspects may be improved for future sessions), which has been found to significantly increase intervention effects compared to trials that did not provide this type of ongoing supervision [10]. This study will use the same procedures for training and supervision as past *Body Project* trials [31, 33].

#### Control condition

An educational control condition was selected to control for expectancy effects and demand characteristics. Pre-existing freely available videos allow participants to view them over the Internet to match the virtual delivery modality (1 h per week over 4 consecutive weeks). The videos contain information about how to promote a positive body image, costs associated with EDs, and how to seek help if they experience concerns related to body image, eating, body pressures, and weight. Past trials of the *Body Project* have utilized such educational videos as the control condition [15, 33, 34]. Results indicated that participants assigned to the educational control condition showed reductions in ED symptoms compared to assessment-only controls [34], but that the reductions in ED symptoms were significantly larger for *Body Project* participants than for control participants. Adherence to watching the videos will be recorded by self-report at posttest assessment. In a previous trial participants showed similar adherence to attending *Body Project* group sessions versus watching the educational videos (typically over 80%) [35].

### Assessment

All measures are translated to Norwegian. Only the Eating Disorder Examination Questionnaire (EDE-Q) and Eating Disorder Assessment for DSM-5 (EDA-5) are validated in Norwegian, while the psychometric properties of the remaining measures are validated in English. See details below:

*Thin-ideal internalization*: the 8-item Ideal-Body Stereotype Scale-Revised (IBSS-R) [36] to assess endorsement of thin-ideal using a Likert scale ranging from 1 = strongly disagree to 5 = strongly agree. It has shown internal consistency (α = 0.91), 2-week test-retest reliability (*r* = .80), predictive validity for future ED onset, and sensitivity to detecting intervention effects [33].

*Body dissatisfaction*: ten items from the Body Parts Scale [37] to assess dissatisfaction with body parts with a Likert scale ranging from 1 = extremely dissatisfied to 6 = extremely satisfied. It has shown internal consistency (α = 0.94), 3-week test-retest reliability (*r* = .90), predictive validity for future ED onset, and sensitivity to detecting intervention effects [33].

*Negative affect*: 20 negative items from the Positive and Negative Affect Schedule – Revised (PANAS-X) [38] to measure negative affect. It has high internal consistency (mean Cronbach’s α of 0.94), test-retest reliability (r = .78), and convergent validity [15].

*ED symptoms*: The Eating Disorder Examination Questionnaire (EDE-Q) [39] is a self-report 28-item questionnaire of specific eating disorder psychopathology based on the Eating Disorder Examination (EDE) diagnostic interview [40]. Reponses range from 0 to 6 with higher scores indicating higher levels of ED psychopathology. The EDE-Q consists of the four subscales *eating restraint*, *eating concern*, *shape concern*, and *weight concern* and is previously translated and validated in Norwegian men and women [41, 42].

*Appearance ideal internalization and pressures*: the Social Attitudes Towards Appearance Questionnaire 4 – Revised (SATAQ-4R) for women [43] consists of 31 items with subscales which measure: internalization thin/low body fat, internalization of muscularity, internalization of general attractiveness, pressures from family, pressures from peers, pressures from significant others, and pressures from media. Internal consistency (Cronbach’s α ≥ 0.82) and construct validity have been demonstrated.

*Implicit attitudes*: the Implicit Association Test (IAT) [44] measures implicit attitudes to the thin beauty ideal. The IAT is a widely used measure of implicit attitudes based on the strength of automatic associations between concepts and positive versus negative adjectives, which assesses attitudes toward images of the thin appearance ideal and words describing ED behaviors. It has shown good psychometric properties [45]. Participants are asked to quickly sort words into categories in a series of seven blocks that vary in whether the thin images and ED words are paired with positive or negative words. Response latencies are recorded according to standard.

*ED diagnoses*: the Eating Disorder Assessment for DSM-5 (EDA-5). The EDA-5 [46] is as a semi-structured, web-based diagnostic interview assessing DSM-5 feeding and eating disorders that have been present in the previous three months. The interview can be administered with limited training [47] and is significantly quicker to administer than traditional diagnostic interviews for EDs. High rates of agreement have been found between diagnoses by EDA-5 and traditional clinical interviews, such as the Eating Disorder Examination (EDE) interview, supporting its diagnostic validity [46, 48]. A recent validation study [48] supports the validity of the Norwegian EDA-5 to efficiently generate ED diagnoses without compromising diagnostic accuracy.

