## Background

EDs affect approximately 13% of women and 5% of males [1, 2], and are marked by chronicity and high rates of relapse, as well as substantial impairment, academic difficulties, depression, anxiety, self-harm, suicide, and morbidity [3, 4]. Risk factors for the development of EDs include female gender, adolescent age, internalization of the thin beauty ideal, body dissatisfaction, dietary restraint, and negative affect [5]. In Norway, results from a recent prevalence study in adolescents revealed that ED psychopathology was common (20%), and that the estimated prevalence of any ED was as high as 16% among adolescent girls [6]. These rates are comparable to those reported in other countries [7]. Yet, less than 20% of affected individuals receive treatment [8]. This underscores the importance of efforts to prevent the development of ED in high-risk populations. Selective ED prevention approaches specifically targets individuals at high-risk for EDs, i.e. young women > 15 years with body dissatisfaction [5].

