## Research aims and hypotheses

The overall objective of this study is to evaluate the effectiveness of the *Body Project*. Specifically, the following hypotheses will be tested:

Participants in both peer-led or clinician-led virtually delivered *Body Project* groups will show significantly greater reductions in ED risk factors and symptoms compared to controls.Participants in both peer-led or clinician-led virtually delivered *Body Project* groups will show a significantly lower rates of ED onset over the 2-year follow-up than controls.Participants in both peer-led or clinician-led virtually delivered *Body Project* groups will show significant reductions in positive implicit attitudes towards the thin ideal compared to controls.Participants in peer-led (young female students) virtually delivered *Body Project* groups will show significantly greater improvements in outcomes than participants in clinician-led virtually delivered *Body Project* groups.

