### Statistical analyses

*Model building.* Intent-to-treat (ITT) analyses of condition effects will be evaluated using mixed effects growth models fit with SAS 9.2 PROC MIXED [50]. Individual variability in outcomes from posttest to 2-year follow-up was modeled adjusting for pretest outcome values. Following Singer and Willet [51], when constructing the longitudinal models we will (a) examine empirical growth plots; (b) fit an unconditional means model; (c) fit an unconditional linear growth model; (d) fit unconditional non-linear models; and (e) compare models of longitudinal change using the Akaike Information Criterion. Condition, time (coded in months since posttest), and a condition × time interaction will be added to the unconditional model. We will estimate a growth model for each continuous outcome. We will report the results of planned contrasts from these models, contrasting each pair of conditions, reporting condition differences in the model implied least-square means derived from the time and condition × time interactions at 1- and 2-year follow-up. We will report effect sizes that are equivalent to Cohen’s *d* [52]. We will use full information maximum likelihood (ML) estimation to impute missing data because this intent-to-treat approach produces more accurate and efficient parameter estimates than alternative analytic approaches such as analyzing only participants who provide complete data, making multiple imputation the recommended procedure for handling missing data [53]. Missing data will be imputed using PROC MI using baseline levels of the outcomes, condition, and demographic factors (age, race, and parent education). Based on the recommendations [53], we will impute 50 data sets. Model parameters and standard errors were combined following Rubin [54] and implemented using PROC MIANALYZE. Cox proportional hazard models, fit with STATA [55] will test whether eating disorder onset over 2-year follow-up was significantly lower in each condition versus each other condition. Schoenfeld residuals will be examined to test the proportional hazards assumption. Hazard ratios and number needed to treat (NNT; [56]) are provided as measures of effect size. Because hazard models accommodate right censoring, we will not impute missing incidence data. Given that 88% of the effects from previous *Body Project* trials have replicated in 22 controlled trials from independent teams [15], we will use a p-value of 0.05 for all inferential tests because this usually balances risk for type I and type II errors.

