
### Power calculation

Sample size calculation was made for incidence of EDs assessed over a 2-year follow up via diagnostic interviews as the primary endpoint. Incidence rates were obtained from the previous Swedish virtual *Body Project* RCT [16]. Based on this trial we postulated a difference in incidence of EDs of 8.8% and 2% between groups, and a hazard ratio of 0.26 during 2 years of follow-up. Then, with a significance level of 5% and a power of 90% the estimated number of patients needed was 147 in each arm, the total number needed was 441.

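### The primary endpoint is eating disorder onset over two years, but the diagnostic interview as described sees only the last three months before the 1- and 2-year visits

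*Protocol article*

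**What the plan says.** Four statements in the protocol article bear on this point.

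- **Endpoint (Power calculation):** "Sample size calculation was made for incidence of EDs assessed over a 2-year follow up via diagnostic interviews as the primary endpoint".
- **Hypothesis (Research aims and hypotheses):** the second hypothesis expects "significantly lower rates of ED onset over the 2-year follow-up than controls".
- **Instrument (Assessment, ED diagnoses):** the EDA-5 is described as a "web-based diagnostic interview assessing DSM-5 feeding and eating disorders that have been present in the previous three months". It is the only source of ED diagnoses that the article describes.
- **Schedule (Procedure):** "ED diagnostic interviews are conducted at baseline, 1-year, and 2-year assessments". The posttest and 6-month assessments carry no diagnostic interview.

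On the analysis, Statistical analyses says that Cox models "will test whether eating disorder onset over 2-year follow-up was significantly lower in each condition versus each other condition", with hazard ratios reported and Schoenfeld residuals examined. The article describes neither a longer look-back at the follow-up interviews nor any dating of onset between them.

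**The concern.** The endpoint is named for a 24-month period, while the stated instrument and schedule observe two short parts of it. Three consequences follow if the interviews are run as described.

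1. An ED that starts after one interview and has remitted more than three months before the next leaves no trace in the primary endpoint.
2. A case that is found is known only to have arisen at some point before the 1-year interview, or between the 1- and 2-year interviews. The Cox model then has two possible event times, and the check of proportional hazards has little to work with.
3. The chance of being counted rises with episode length, so the endpoint reflects duration as well as onset. An arm in which episodes are shorter would show fewer cases even if as many women fell ill.

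This is a matter of data collection. An analysis plan cannot later recover episodes or dates that nobody asked about, so the time to act is before the follow-up interviews are held.

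**Working it through.** **Inputs from the article.** Look-back of 3 months (Assessment). Follow-up interviews at 1 and 2 years, taken here as months 12 and 24 (Procedure). Planning rates of 8.8% and 2% over two years, hazard ratio 0.26, 5% significance, 90% power and 147 per arm (Power calculation).

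**The plan's own figure.** At 147 per arm, one two-arm comparison expects 147 × (0.088 + 0.02) = 15.9 events. Schoenfeld's formula, two-sided, requires 4 × (1.960 + 1.282)² / (ln 0.26)² = 23.2 events for 90% power, and 15.9 events give about 77%. The stated 90% was therefore not reproduced. That is a separate matter, and nothing below depends on it.

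**Step 1: coverage.** Two interviews × 3 months = 6 months seen (months 9–12 and 21–24). 24 − 6 = 18 months lie outside the windows (months 0–9 and 12–21).

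**Step 2: which episodes are missed.** An onset outside a window is still counted if the episode lasts until the window opens. Only episodes that both begin and remit inside one of the two gaps are missed. The longest wait for a window is nine months, so an episode of nine months or more is always caught.

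**Step 3: share of onsets detected.** Assumptions, none of them from the documents: onset uniform over time, one episode per woman, and any overlap with a window counts as detected. The two 12-month intervals are alike, so one suffices.

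- Exponential duration with mean D months: P = [3 + D(1 − exp(−9/D))] / 12.
- Fixed duration D, up to 9 months: P = (3 + D) / 12; beyond that, P = 1.

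| Duration D (months) | Exponential, mean D | Fixed at D |
|---|---|---|
| 3 | 0.488 | 0.50 |
| 6 | 0.638 | 0.75 |
| 12 | 0.778 | 1.00 |
| 24 | 0.875 | 1.00 |

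**Step 4: effect on the rates.** Suppose that 8.8% and 2% were true incidences and that duration were the same in both arms. The observed rates under exponential durations of mean 3, 6, 12 and 24 months would be 4.3%/1.0%, 5.6%/1.3%, 6.8%/1.6% and 7.7%/1.8%. Both arms are multiplied by the same P, so the risk ratio stays at 0.02/0.088 = 0.23.

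**Step 5: effect on the comparison if duration differs.** With the same true onset rate in both arms, the apparent risk ratio is the ratio of the two detection shares.

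- Mean 6 versus 12 months: exponential 0.638/0.778 = 0.82; fixed 0.75/1.00 = 0.75.
- Mean 3 versus 12 months: exponential 0.488/0.778 = 0.63; fixed 0.50/1.00 = 0.50.

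**The case against.** The strongest reply is that a journal article condenses. Assessment describes the EDA-5 as an instrument; it does not say that interviewers never ask about earlier months. A full protocol or interviewer manual may provide for that and for dating onset. This stands as a possibility. But the article does state the three-month window and the visit schedule next to a two-year endpoint, and what it states does not fit together. If a longer look-back exists, the remedy is to say so.

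Several stronger readings are tempting, and the documents do not support them.

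- **Three quarters of cases are lost.** The 18 uncovered months are time, not cases. Background says that EDs "are marked by chronicity and high rates of relapse". Chronicity favours detection, and a woman whose first episode is missed may be counted through a later one.
- **The trial will see fewer events than planned.** The 8.8% is a rate taken from the earlier Swedish trial, whose interview window and schedule the article does not describe. If ascertainment there was similar, the loss is already inside that figure.
- **Hypothesis 2 cannot be answered.** Misses that are equal across arms leave the risk ratio about unchanged (Step 4). Spurious prevention requires the intervention to shorten episodes. The article reports larger symptom reductions in participants with an ED than in those without (d = 0.71 versus 0.17), which makes an effect on the course of illness conceivable, but it gives nothing on duration. Even a fourfold shortening yields ratios of 0.50 to 0.63, far from the planned 0.26.
- **Relapses are wrongly counted as onsets.** The hypothesis speaks of ED onset, not of first lifetime onset, and randomisation balances prior history in expectation.
- **The trial measures only 3-month prevalence at two visits.** If baseline cases are set aside, what is observed is first detection at either of two windows. That is closer to incidence than prevalence is, though still not full two-year incidence.

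It is also fair to say that the three-month interview is the form the article supports with validation, in Norwegian as well, so a longer look-back has a price.

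**Conclusion.** The mismatch is real and should be fixed, but it does not invalidate the trial. As written, EDs that begin and remit wholly within months 0–9 or 12–21 are not recorded, and onset is known only to one of two visits while a Cox model is planned.

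The size of the loss cannot be fixed from the documents because they give no episode duration. Under the stated assumptions, detection ranges from about 49% to 88% of onsets for exponential durations of mean 3 to 24 months, and reaches 100% if every episode lasts nine months or more. Whether the event rate falls below 8.8% is unknown. Dependence of detection on duration means that an effect on episode length could appear partly as prevention of onset. The ratios of 0.82 and 0.63 illustrate how far that could go and are not a forecast.

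**What to change.** **Preferred.** At the 1- and 2-year interviews, keep the EDA-5 three-month diagnosis as it stands and add questions, put by the masked interviewer, that cover the whole interval since the previous interview. Record the month in which diagnostic criteria were first met and use it as the Cox event time. Report the three-month definition as a sensitivity analysis.

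*Cost:* a few added questions at visits already planned, and protocol wording. The drawback is that recall over up to 12 months is less accurate than over three, and the added questions go beyond the window for which the article describes the instrument. That is why the three-month result should be reported alongside.

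**If the three-month window alone is kept.** Define the endpoint as a new ED present in the three months before the 1- or 2-year interview, analyse it with a discrete-time or interval-censored model, and do not call it full two-year incidence.

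*Cost:* wording and a change of model. This makes the endpoint accurate but does not recover episodes that fall between the windows.

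If the full protocol already has a longer look-back or dates onset, state that wherever the endpoint and the interview are described.

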### Implementation fidelity and facilitator competence

All sessions will be recorded and key elements of a randomly selected subset of sessions will be rated for degree of fidelity (100-point scale from 0 = No adherence; the section was skipped to 100 = Perfect; all material in the section was presented as written). Facilitator competence will be rated with 12 items (e.g., leaders express ideas clearly and at an appropriate pace) using a 100-point scale with anchors for each item (e.g., 20 = Poor; leaders are difficult to follow and session proceeds at an uncomfortable pace, 100 = Superior; leaders are unusually articulate and express ideas in ways that all group members understand; perfect pace). Fidelity ratings and competence ratings have shown inter-rater agreement (ICC = 0.92 and = 0.96, respectively) for the original *Body Project* [49]. The PI will be responsible to do these ratings and provide supervision to group facilitators.

